#### Father

When the father attends for one of the research ultrasounds, consent will be sought to take blood by an appropriately trained member of staff, such as a research midwife or research sonographer.

The following are some of the key points to be raised during the consent process:

Participation in the study is voluntary, consent can be withdrawn at any time during the study and withdrawal will not affect their routine care.The purpose of the study.The requirements of participating in the study.All information will be treated as strictly confidential.These analyses could include genetic studies and studies done by commercial entities.We will not report any result that allows identification of your baby’s paternity.

Information relating to data handling and biological samples is detailed below.

#### Randomised controlled trial

Eligible women will be consented by an appropriately trained and qualified member of the research team, for example, a sonographer or a research midwife. If for any reason recruitment to the RCT element of the study is not possible (eg, in the unlikely event of failure of the machine which performs the soluble fms-like tyrosine kinase receptor-1 (sFLT1) and placenta growth factor (PlGF) assays), women will still have their 36 wkGA scan and blood sample for the cohort element of the study. For women who are approached to consent to the RCT, the discussion will include the following information:

The blood sample will be analysed using a test which is believed to indicate the health of the placenta.The blood test is in use in other clinical situations but it is not currently recommended as a screening test, that is, it is currently only used in situations where a woman has a problem.We have evidence that the test, when combined with the scan results and the mother’s own past history, identifies women at an increased risk of complications.The aim of the study is to determine whether performing the test and acting on the results leads to a lower rate of complications.Consenting to the study means that we will perform the test on her blood sample.If she is deemed high-risk on the basis of the test, she will then be randomised to routine care or to being contacted to discuss how to manage the increased risk of complications.The main intervention will be to offer earlier delivery of the baby by induction of labour.This will be offered from 37+0 and will be strongly recommended no later than 39+0. Delivery at 37 wkGA will be strongly recommended if the blood test and/or scan were very strongly suggestive of a problem.If she screens positive and is randomised to intervention, she will be contacted within 7 days or fewer.About 3–4 women per 100 will be contacted.She should not assume that she is low risk if she is not contacted, as some women (about 3–4 women per 100) will have screened high-risk and been randomised to routine care.Hence, if she has any concerns about any aspect of the pregnancy (eg, her baby’s movements, bleeding, symptoms), she should contact her midwife or doctor as she normally would.Not being contacted by the research team does not mean that she can assume that she is not at risk of complications.

The signed consent form has three copies, one will be retained for the study records, one placed in the patient’s hand-held notes and the third study copy will be scanned for recording in EPIC. A letter will be sent to the woman’s GP informing them of participation in the RCT element of the study.

### Additional consent provisions for collection and use of participant data and biological specimens

#### Cohort study

The following are key points to be raised during the consent process for recruitment to the cohort:

Participation will involve research staff accessing medical notes and linking electronic clinical records to their research data, including longer term outcomes (such as subsequent pregnancies (mother) and educational outcomes (child)).Their personal identifiable information will be held securely. Their clinical and research data will only be shared with other researchers if we are certain that it is anonymous and that they cannot be identified.They are providing broad consent for the analysis of their blood and other samples, to be used in any way that enhances our understanding of normal and complicated pregnancy and how this influences health and well-being in later life.These analyses could include genetic studies and studies done by commercial entities.

### Interventions

Eligible women who consent to the RCT element of the study will have the sFLT1:PlGF ratio (the concentration of soluble fms-like tyrosine kinase receptor 1 divided by the concentration of PGF, measured on a Roche Cobas assay platform^10^) measured in their 36 wkGA serum sample. The risk status will be based on the combination of the exact level of the ratio plus other maternal characteristics and ultrasound scan findings.

Screen positive will be defined as≥1 of the following:

sFLT1:PlGF ratio >110.sFLT1:PlGF ratio >38+36 wkGA ultrasonic estimated fetal weight (EFW) <10th percentile.^11^sFLT1:PlGF ratio >38+20 wkGA uterine artery Doppler pulsatility index >90th percentile.^10^sFLT1:PlGF ratio >38+ increased risk of pre-eclampsia using an adapted version of NICE Guideline Antenatal Care defined as ≥1 of the following:Chronic kidney disease.Autoimmune disease, such as systemic lupus erythematosus or antiphospholipid syndrome.Type 1 or type 2 diabetes.Chronic hypertension.Age 40 years or older.Body mass index ≥35 kg/m² at first visit.

Screen positive women will then be randomly allocated to (a) revealing the result with review by a doctor (usually a consultant in maternal-fetal medicine) or (b) masking the result, with the consequence that the woman receives the same care that she would have received had she not participated in the RCT. Women will be randomised using a computerised system employing stratification on the basis of the four main elements of the risk assessment. The rationale for the choice of the two groups for comparison is that women who have the result masked will have pregnancy care as if they had not had the screening test at all. We will then be able to compare the intervention group with the high-risk masked group to determine whether revealing the result and changing clinical care on the basis of the result reduced the risk of the primary outcome. The study design also allows us to compare outcomes among the women who screened high-risk but were randomised to masking of the result with the women who screened low risk. This comparison will allow assessment of how well the screening approach performs in identifying high-risk women in this population.

### Intervention description

Women who screen positive and are randomised to the intervention arm will be assessed as soon as possible thereafter, with the aim of conducting the assessment within 7 days of the blood sample being obtained. The primary intervention is to offer induction of labour with weekly monitoring and to re-offer induction of labour for women who decline. The recommended timing of the induction of labour will depend on which elements of the screening assessment were positive. Women with extreme elevation of the ratio (>110) or those with an elevated ratio (>38) plus a baby that is small for gestational age (SGA) on ultrasound (EFW <10th percentile) will be recommended to have induction of labour at 37 weeks. All other women will be recommended to have induction of labour at 39 weeks. The doctor assessing the patient will have access to a report containing the results of the screening assessment. For the purposes of the study, the Rosie Hospital has a clinical guideline for the management of screen positive women in the trial and this is available to all staff through the hospital’s intranet.

### Criteria for discontinuing or modifying allocated interventions

The allocated intervention will be either routine care or to reveal the screening test result and to make a recommendation around the timing of induction of labour, and these would apply in all situations. However, a control participant may be recommended to have induction of labour for some other reason, as part of their routine clinical care. Conversely, intervention participants can decline the offer of induction and await the spontaneous onset of labour.

### Strategies to improve adherence to interventions

The medical staff who see high-risk participants randomised to intervention will generally be sub-specialist consultants in maternal-fetal medicine who have had training about the study and are fully acquainted with the details of the clinical guideline. Compliance with the guideline can be assessed at the time of analysis as we predict that the interval from the fourth research visit and birth will be shorter in the intervention group due to the recommendation to induce labour between 37+0 and 39+0 weeks.

### Relevant concomitant care permitted or prohibited during the trial

All other aspects of the care of participants will be as per Rosie Hospital clinical guidelines and no specific care will be mandated or prohibited by participation in the study.

### Provisions for post-trial care

The trial team aims to see each participant who is randomised to intervention in the postnatal period and during the delivery episode, although this may not always be possible. The purpose of the visit will be to check on the patient’s well-being and to answer any questions they have in relation to their care. In relation to compensation for harm, Cambridge University Hospitals NHS Foundation Trust, as a member of the NHS Clinical Negligence Scheme for Trusts, accepts full financial liability for harm caused to participants in the study caused through the negligence of its employees and honorary contract holders. The University of Cambridge has an insurance policy in place for negligent harm caused as a result of protocol design and for non-negligent harm arising through participation in the study.

### Outcomes

The study has two primary outcomes and both are composites. The first is one or more of the following: (a) diagnosis of pre-eclampsia (using the ACOG 2013 definition^12^), (b) perinatal death or perinatal morbidity or (c) delivery of an infant with a birth weight <3rd percentile for sex and gestational age. Perinatal death is defined as stillbirth or neonatal death. Perinatal morbidity is defined as one or more of the following: a 5 min Apgar score <7, delivery with metabolic acidosis (defined as an umbilical cord artery or vein pH<7.1 and a base deficit of >10 mmol/L) or admission to the neonatal unit (defined as admission <48 hours after birth and discharge ≥48 hours after admission), that is, either the special care baby unit (SCBU) or the neonatal intensive care unit (NICU). The second primary outcome is a subgroup of the first and is defined as one or more of the following: (a) pre-eclampsia with severe features (ACOG 2013 definition^12^) or (b) perinatal death or severe perinatal morbidity. Severe perinatal morbidity is defined as live birth associated with hypoxic ischaemic encephalopathy (any grade), use of inotropes, mechanical ventilation or severe metabolic acidosis (defined as an umbilical cord artery or vein pH<7.0 and a base deficit of >12 mmol/L).

Secondary outcomes will include each of the individual elements of the maternal and perinatal composite described above. The following additional secondary outcomes will be studied, based on a previous trial of term induction of labour, the 35/39 trial.^13^

Maternal: (a) maternal death, (b) maternal stroke, (c) maternal admission to any medical unit (eg, intensive care unit, stroke unit, coronary care unit, neurosciences critical care unit), (d) placental abruption, (e) cord prolapse, (f) caesarean section, (g) epidural anaesthesia, (h) instrumental vaginal delivery, (i) general anaesthesia, (j) postpartum haemorrhage (any >500 mL), (k) postpartum haemorrhage requiring blood transfusion, (l) infection (pyrexia >38°C and treated with a course of antibiotics).

Perinatal: (a) Apgar score at 1 min, (b) Apgar score at 5 min, (c) Apgar score at 10 min, (d) umbilical arterial pH and base deficit, (e) umbilical vein pH and base deficit, (f) any/duration of admission to SCBU, (g) any/duration of admission to NICU, (h) fracture (any), (i) seizures (any), (j) prolonged hypotonia (>2 hours), (k) abnormal level of consciousness (hyperalert, drowsy, lethargic, stupor, decreased response to pain, coma), (l) tube feeding (any duration), (m) head cooling, (n) phototherapy, (o) severe hypoglycaemia (defined as requiring parenteral treatment or drug therapy), (p) birth weight, (q) birth weight percentile for sex and gestational age, (r) stage of hypoxic ischaemic encephalopathy, (s) oxygen administration and/or respiratory support. All diagnoses relate to the delivery admission, that is, all events until discharge of the mother or baby.

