## Introduction

### Background and rationale

 Maternal and perinatal deaths account for 6%–7% of all deaths globally, approximately equivalent to half of the global burden of deaths caused by cancer.^1^ Placental dysfunction is implicated in the aetiology of many of the associated conditions, including pre-eclampsia, fetal growth restriction (FGR), spontaneous preterm birth and stillbirth.^2^ The approaches to screening for these outcomes include methods which are relatively crude and ineffective. For example, the UK’s National Institute for Health and Care Excellence (NICE) recommended method of screening for FGR is to measure the external size of the uterus with a tape measure, despite the fact that surveillance based on this approach has a sensitivity to detect small infants of ~20%.^3^ An alternative is to perform late pregnancy ultrasonic fetal biometry in all women. However, a meta-analysis of eight randomised controlled trials (RCTs) of universal ultrasound recruiting ~35 000 women showed no evidence of benefit.^4^ Implementation of universal late pregnancy ultrasound in France was associated with dramatic increases in morbidity in false positives, principally through iatrogenic prematurity.^5^

In a 2012 review in *PLoS Medicine*,^6^ we outlined key methodological weaknesses in the literature:

Screening tools were evaluated in interventional trials in the absence of high quality information on their diagnostic effectiveness.Screening tests were not coupled to an effective intervention.Trials were underpowered.

The review proposed a plan to generate novel clinically effective methods of screening:

Trials should be preceded by high quality studies of diagnostic effectiveness.Initial efforts should focus on screening for complications at term.The most efficient trial design is to screen all women and randomise high-risk women to intervention or routine care.Initial efforts should focus on nulliparous women,^7^ as they have a higher a priori risk of adverse pregnancy outcome. They lack information on complications during previous pregnancies,^8^ one of the most discriminating predictors of pre-eclampsia and FGR.

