### Plans to promote participant retention and complete follow-up

Outcome data will be collected from all participants, irrespective of any deviation from the intervention protocol. For women who screen low risk or who screen high-risk and are randomised to routine care, there will be no further study visits after the 36 wkGA visit. All women will deliver their baby within 8 weeks of this visit, hence we do not anticipate substantial loss to follow-up. If women choose to deliver in a different hospital, we will liaise with the hospital in question to retrieve their outcome data. Women who screen high-risk and are randomised to intervention will typically be offered a face to face consultation with a consultant in maternal-fetal medicine within a week of their 36 wkGA visit. Ongoing care will be informed by a Clinical Guideline for high-risk participants, which has been incorporated into the hospital’s Clinical Guidelines database. Ongoing care will be determined in a process of shared decision-making between the consultant and the high-risk participant, who will be able to choose to accept or decline elements of care, such as early delivery or enhanced maternal and fetal monitoring.

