### Data management

Outcome data will be collected by multiple methods. Research staff will access the participant’s records on EPIC to obtain outcome data. Information will be entered onto a standardised paper form and paper records will be subsequently transferred to a research database. Transcription of data into an electronic format will use double entry with checking of anomalous values. The data will be intermittently reviewed to assess completeness and to identify outliers, which will then be checked. Outcome data will also be collected by downloading the electronic data from participants from the different software packages used by CUHFT to store clinical information. This may include download of information from the main EMR, EPIC (eg, laboratory records, vital signs, point of care testing and notes for free text searching), ultrasound data (Astraia) and neonatal outcome data (Badgernet). Outcome data will be obtained from external Trusts in the event that a woman transfers her care after 36 wkGA. Long term outcomes will be ascertained through linkage of the mother’s or baby’s records (eg, for outcome of subsequent pregnancy, future inpatient or outpatient care (mother and baby) and educational achievement (baby only)). Examples of external data sources include NHS Digital, Public Health England and the Department for Education.

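### Outcome capture ends at discharge from the delivery admission, so the primary comparison cannot separate pre-eclampsia prevented from pre-eclampsia deferred past discharge

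*Protocol article*

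**What the plan says.** All places are in the protocol article.

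- **Outcomes, last sentence:** "All diagnoses relate to the delivery admission, that is, all events until discharge of the mother or baby". It follows the definitions of both primary composites and the secondary lists, and nothing limits it to the secondary outcomes. No fixed number of days after birth is given.
- **Outcomes, first primary:** pre-eclampsia, birth weight below the 3rd percentile, or perinatal death or morbidity. The second primary contains pre-eclampsia with severe features. Neither pre-eclampsia component has a time limit of its own. The neonatal-unit component does: "defined as admission <48 hours after birth and discharge ≥48 hours after admission". For death, "Perinatal death is defined as stillbirth or neonatal death", again without a time limit.
- **Strategies to improve adherence to interventions:** the authors predict that "the interval from the fourth research visit and birth will be shorter in the intervention group".
- **Sample size:** for women meeting the 37-week criteria, 25%, 50% and 75% of pre-eclampsia cases are taken as prevented, depending on when they occur, and 40% of growth-restriction cases. For women meeting the 39-week criteria, only pre-eclampsia is taken to fall. In all, 51 of 126 events are assumed prevented.
- **Plans to promote participant retention and complete follow-up:** "All women will deliver their baby within 8 weeks of this visit". Routine-care women have no study visit after 36 weeks.
- **Data management:** outcome data come from EPIC and Badgernet. "Long term outcomes will be ascertained through linkage of the" records of mother or baby, with later inpatient care among the examples. This linkage is not tied to the primary or secondary outcomes.

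**The concern.** The window closes at an event that follows birth, and the intervention changes when birth happens. Birth weight, Apgar score, cord gases and stillbirth are settled by birth, so the discharge rule cannot affect them. Pre-eclampsia is different. If a woman is delivered before the disease shows itself and is first diagnosed after she goes home, she is recorded as event-free. Had she stayed pregnant under routine care, the same disease might have been diagnosed before birth and counted.

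The planning assumptions treat antenatal cases avoided by earlier birth as prevented and make no allowance for cases that surface after discharge. In the 39-week group the whole assumed benefit rests on this component. A positive result on either primary could then be read as prevention when part of it is deferral.

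Separately, the Background describes a national programme of universal late ultrasound as "associated with dramatic increases in morbidity in false positives, principally through iatrogenic prematurity". Harm from earlier birth is thus a stated worry, yet infant readmission is not a listed outcome, and secondary neonatal outcomes such as phototherapy and tube feeding are counted only to discharge.

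**Working it through.** **Inputs (Sample size section).** Control risk 0.49 (126/256 = 0.492); intervention risk 0.29; RR = 0.29/0.49 = 0.592; 246 women for 90% power at two-sided 0.05; 250 women (125 per arm) for 85% power at alpha 0.025; no loss to follow-up. Post-discharge rates are **not** in the documents; those below are assumptions.

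**Step 1. Reproduce the plan's figures.** Pooled-variance normal approximation, no continuity correction:

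n per arm = [z(1−α/2)·√(2·p̄·q̄) + z(power)·√(p1·q1 + p2·q2)]² / (p1 − p2)²

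With p̄ = 0.39: [1.960·√0.4758 + 1.282·√0.4558]² / 0.04 = 122.9, so 123 per arm and 246 in total, an exact match. Power with 184 women is 79.9% (stated about 80%). With 250 women at alpha 0.025:

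Power = Φ{[√125·0.20 − 2.241·√0.4758] / √0.4558} = Φ(1.022) = 84.7% (stated 85%).

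**Step 2. Equal missed rate r among women event-free at discharge, both arms.** Control risk becomes 0.49 + 0.51r and intervention risk 0.29 + 0.71r.

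**Step 3. Misses in the intervention arm only.** Intervention risk becomes 0.29 + e, which is 1.25 to 6.25 of 125 women for e = 1 to 5 points. Control risk stays at 0.49.

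| Assumption | Control | Intervention | True RR | Power, N = 250, alpha 0.025 |
|---|---|---|---|---|
| None missed | 0.490 | 0.290 | 0.592 | 84.7% |
| r = 1% | 0.495 | 0.297 | 0.600 | 83.6% |
| r = 2% | 0.500 | 0.304 | 0.608 | 82.6% |
| r = 3% | 0.505 | 0.311 | 0.616 | 81.5% |
| r = 5% | 0.516 | 0.326 | 0.631 | 79.3% |
| e = 1 point | 0.490 | 0.300 | 0.612 | 80.2% |
| e = 2 points | 0.490 | 0.310 | 0.633 | 75.0% |
| e = 3 points | 0.490 | 0.320 | 0.653 | 69.3% |
| e = 5 points | 0.490 | 0.340 | 0.694 | 56.6% |

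In every row the endpoint as defined would still show RR 0.592. The power column refers to an endpoint that includes the missed cases, not to the protocol's own endpoint.

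**Step 4. When would the RR be unaffected?** Let r(I) and r(C) be the missed rates among event-free women in the intervention and control arms. Setting (0.29 + 0.71·r(I)) / (0.49 + 0.51·r(C)) = 0.29/0.49 gives r(C)/r(I) = (0.71 × 0.49)/(0.51 × 0.29) = 2.35. Below that ratio the recorded RR overstates benefit; above it, the recorded RR understates benefit.

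**Step 5. Death and readmission.** The Outcomes section counts neonatal death without a time limit, then ends all diagnoses at discharge. A neonatal death at home is in under the first statement and, if death is covered by the second, out under it. Readmission belongs to neither composite, and the 48-hour admission rule excludes late neonatal-unit admission in both arms.

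**The case against.** The strongest reply is that the rule is the same in both arms, so bias comes only from a difference in missed events, and the documents give no rate for either arm. That stands as to size and direction. A reader might infer that benefit *is* overstated; the documents do not show that. Sameness alone does not remove the problem, though: by Step 4, equal missed rates still pull the recorded RR away from 1, because more intervention women are event-free at discharge. The shift is then small.

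A reader might also infer that readmissions of early-born infants count as prevented events. They do not, since readmission is in neither composite. Nor can one say that deaths after discharge are simply lost: the definition of perinatal death has no discharge limit, and the Adverse event reporting section makes neonatal and maternal death reportable in both randomised groups. Harm of early birth is partly covered by the secondary list, and the Background's example concerns a different programme.

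A fixed postpartum window also starts at birth, so it too ends sooner after randomisation in the intervention arm. True, but it no longer depends on length of stay, and it brings deferred cases into view. The trial team aims to see intervention women postnatally (Provisions for post-trial care) and plans no such contact for routine care. Longer capture could therefore detect cases unequally, and that caution stands.

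Last, a sensitivity analysis may already be in the SAP, which is not shown. The point here is the discharge rule that the article does state.

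**Conclusion.** The concern holds in a limited form. The discharge rule scores later pre-eclampsia as no event, and the intervention acts on the timing of birth. The primary comparison as defined therefore cannot separate prevention from deferral. An overstated benefit is plausible but unquantified. Under the assumed rates the true RR would be 0.60–0.63 with equal missed rates of 1–5% among event-free women, or 0.61–0.69 with 1–5 points missed in the intervention arm only; the second range is the unfavourable extreme. These figures assume that pre-eclampsia can first be diagnosed after discharge and that the planned 49% and 29% hold for events up to discharge. The article does not say how many of the 51 prevented events are pre-eclampsia and gives no planning rate for the second primary, so its exposure cannot be sized.

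It would be wrong to conclude that the trial is underpowered: the stated sample size and power reproduce for the endpoint they describe. The missing readmission outcome is a gap in harm capture and not a bias in either primary. The treatment of neonatal death, and whose discharge ends the window, are wording conflicts to settle whatever the size of the bias.

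**What to change.** Keep the primary definition; changing it with recruitment nearly complete is hard to justify. Before unblinding:

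1. Pre-specify a sensitivity analysis of both primary outcomes that counts pre-eclampsia to the same fixed postpartum time in both arms (for example 6 weeks) and neonatal death to 28 days. If the SAP already has this, a cross-reference is enough.
2. Report infant readmission to 28 days by arm as a safety outcome.
3. State that maternal events run to the mother's discharge and infant events to the baby's.
4. Reconcile the unlimited definition of neonatal death with the discharge limit.

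Items 1 and 2 can use the EPIC, Badgernet and linked inpatient data already named under Data management. The investigators still cannot identify high-risk controls, so these definitions can be fixed without knowledge of results by arm.

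Costs: some extra extraction, for outcomes otherwise abstracted onto paper forms with double entry. Readmissions to other hospitals depend on linkage whose timing is not given. Postnatal contact aimed at intervention women only could make detection unequal, and the report should say so when interpreting the sensitivity analysis.
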